### Participant timeline [13]

The process of enrolment (eligibility screen, informed consent, basic sociodemographic data) will take place in the first 2 weeks after initial injury. At t1, before the 6-week intervention, participants will be allocated and there will be psychometric questionnaires as well as all strength, postural control, gait/run, and jump testing. The same will be done at t2 after the intervention. While t3 is just a follow-up done by email, t4 includes the full diagnostic standard as in t1 and t2 (Fig. 1).

**Fig. 1 Fig1:**
[figure not shown]
Schedule of enrolment, interventions, and assessments

### Sample size [14]

The sample size was calculated for the primary outcome (CAIT) and a repeated-measurement ANOVA with G*Power [42]. Therefore, the following assumptions were used: effect size *f* = 0.5, *α* = 0.05, statistical power (1 − *ß* = 0.80), two groups (SMART and NORMT), and four measurements (t1, t2. t3, t4). The effect size was set according to Wright et al. [43]. This resulted in a total sample size of 82 patients (2 × *n* = 41). With an accounted lost to follow-up of 20%, a sample size of 102 (2 × *n* = 51) is necessary to prove statistic group differences.

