## Assignment of interventions: allocation

### Sequence generation [16a]

We created a randomization plan using a computer-generated randomization schedule (https://www.graphpad.com/quickcalcs/randomize1/) to create a simple balanced randomization. Participants will be randomly assigned to either control or experimental group with a 1:1 allocation (2 × 41 for SMART and NORMT). Subsequent allocation is provided in a separate document that is unavailable to the sport scientist who is performing the enrolling.

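### The protocol gives two randomisation totals: 102 (2 × 51) under sample size and 82 (2 × 41, the number before allowance for loss) under sequence generation

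*Protocol article*

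**What the plan says.** **Protocol article, Sample size [14].** The calculation is for the CAIT under a repeated-measures ANOVA, with two groups and four time points. Its result is "This resulted in a total sample size of 82 patients", or 41 per arm. The section then allows for loss ("With an accounted lost to follow-up of 20%, a sample size of 102") and concludes that "a sample size of 102 (2 × *n* = 51) is necessary to prove statistic group differences".

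**Protocol article, Sequence generation [16a].** "Participants will be randomly assigned to either control or experimental group with a 1:1 allocation". The bracket that follows gives the size of the plan as 2 × 41 for SMART and NORMT.

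**Protocol article, Recruitment [15].** Randomisation and inclusion follow MRI confirmation, so later losses come out of the randomised patients.

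**Protocol article, section [20c], primary study aim.** Participants who withdraw are left out of the primary analysis.

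**The concern.** An inflated sample size is useful only if that many patients are randomised. Here the per-arm number in the randomisation section is the evaluable requirement (41), not the inflated number (51). Someone setting up or auditing the allocation list from that section would prepare 82 assignments; someone working from the sample size section would prepare 102.

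The choice matters because the primary analysis drops withdrawals, so each one reduces the evaluable count directly. If the smaller figure governs, the 20% allowance has been calculated but not used. Generating further assignments once an 82-place list is exhausted would also be an unplanned step in the randomisation.

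The rounding of the inflated figure is a much smaller matter of presentation.

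**Working it through.** **Inputs.** Required evaluable patients: 82 (41 per arm), loss 20%, inflated total 102 (51 per arm), all from Sample size [14]. Randomisation plan: 2 × 41, from Sequence generation [16a]. Withdrawals excluded: section [20c], primary study aim. I assume that patients lost to follow-up are handled as withdrawals.

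**1. Reproducing the protocol's inflated figure.** Formula: N / (1 − d).
- Total: 82 / 0.80 = 102.5.
- Per arm: 41 / 0.80 = 51.25.

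The protocol's 102 (2 × 51) is this result with the fraction dropped. The formula is the right one; the common mistake N × (1 + d) would give 82 × 1.2 = 98.4.

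**2. Evaluable patients under each total.** Formula: N × (1 − d), with d = 0.20.

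| Number randomised | Expected evaluable, total | Per arm | Against the required 82 |
|---|---|---|---|
| 82 (2 × 41), sequence generation | 65.6 | 32.8 | −16.4 |
| 102 (2 × 51), sample size | 81.6 | 40.8 | −0.4 |
| 104 (2 × 52), rounded up to equal arms | 83.2 | 41.6 | +1.2 |

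**3. The loss each total can absorb.** Formula: 1 − 82/N.
- N = 82: 1 − 82/82 = 0%.
- N = 102: 1 − 82/102 = 20/102 = 19.6%.

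In whole patients, losing 10 of 51 in an arm leaves 41. It takes 11 losses (11/51 = 21.6%) to fall to 40.

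**4. Illustration of power.** The section states "effect size *f* = 0.5" and a power of 0.80, but does not give the correlation between measurements or say which ANOVA effect was powered. Among the settings tried, one returns exactly 82: the between-groups effect with f = 0.25 and correlation 0.5, both assumed. The noncentrality is λ = f² × N × m / (1 + (m − 1)ρ), with m = 4 and ρ = 0.5, and the F test has 1 and N − 2 degrees of freedom. At N = 82, λ = 0.0625 × 82 × 4 / 2.5 = 8.2.

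| Evaluable patients | Power |
|---|---|
| 82 | 80.8% |
| 81.6 | 80.6% |
| 81 | 80.3% |
| 65.6 | about 71% |

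In this setting the rounding costs about 0.2 percentage points (80.8 − 80.6) and leaves power above 80%. Randomising only 82 costs nearly 10 points. The illustration depends on f = 0.25. With the stated f = 0.5 and the same correlation, 22 patients would already reach 80% for this effect, so the table does not describe the trial's power under its own stated effect size.

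**The case against.** **On the two totals.** The 2 × 41 may simply repeat the evaluable target, or be a slip carried over from the line before inflation, while the real list may hold 102 or more places. That is possible. A reader might infer that only 82 patients will be randomised and that the trial is therefore underpowered. The document does not support that: it does not show the list, the sample size section clearly calls 102 necessary, and power under the stated effect size is not shown to fail. What stands is narrower. The bracket is attached to the sentence on random assignment, it gives a number that differs from the enrolment target, and nothing in the article reconciles them.

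**On the rounding.** A reader might infer from 102.5 becoming 102 that the sample size is wrong, or that each arm ends one patient short. Neither holds. Losing 20 of 102 leaves exactly 82, and 20/102 = 19.6% rounds to the stated 20%. The expected shortfall is 0.2 patient per arm, and an assumed loss rate is not known to half a percentage point. Rounding up is the usual convention, but nothing in the analysis or the conclusions turns on it here.

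**On relevance.** The two-totals conflict does not come from the rounding and would remain if the sample size section had said 104. That is correct, and it is why the conflict is the main point and the rounding a footnote to it.

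**Conclusion.** The contradiction is real. The sample size section sets the number needed at 102 (2 × 51), and the sequence generation section sizes the randomisation plan at 82 (2 × 41). If the smaller figure were followed, about 66 patients would be evaluable at the stated loss instead of 82, and the allowance for loss would have no effect. This assumes that the 20% loss applies to randomised patients and that those lost are excluded as withdrawals. It does not depend on how the 82 was derived.

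The rounding is arithmetically true but immaterial: 0.4 patient in total. The overall severity is low, because the protocol already contains the larger target and only the text, and possibly the list, must be brought into line.

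**What to change.** 1. In Sequence generation [16a], replace 2 × 41 with the inflated target in Sample size [14], now 2 × 51.
2. Confirm that the computer-generated list covers that number. If it stops at 82, extend it by a documented procedure that keeps the allocation concealed from the person enrolling.
3. In Sample size [14], add one sentence on rounding: either that 102 (2 × 51) keeps 82 evaluable up to 19.6% loss, or that 104 (2 × 52) is planned for a full 20%. Use the chosen total in both sections.

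The cost is two sentences and a check of the list. Keeping 102 adds no patients to the enrolment already stated; choosing 104 adds two. The planned analysis does not change.

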### Recruitment [15]

Participants will mainly be recruited through the emergency department and a cooperating outpatient medical center. All patients with acute LAS (ICD-Code S93.4x) are screened as a potential participant of the study. Patients without ankle fractures (investigated through X-ray) are filtered by further inclusion criteria and contacted by the sport scientists. The patients are specifically asked for their current symptoms. Only if two out of the three criteria (pressure pain on the lateral ankle/ swelling on the lateral ankle/ pain during activities of daily life) are met, additional MRI diagnostics is warranted (not part of standard diagnostic for ankle sprains in Germany). Confirmation of LAS by MRI scans finally leads to patient randomization and inclusion into the study.

## Assignment of interventions: allocation

### Sequence generation [16a]

We created a randomization plan using a computer-generated randomization schedule (https://www.graphpad.com/quickcalcs/randomize1/) to create a simple balanced randomization. Participants will be randomly assigned to either control or experimental group with a 1:1 allocation (2 × 41 for SMART and NORMT). Subsequent allocation is provided in a separate document that is unavailable to the sport scientist who is performing the enrolling.

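### The allocation section gives 2 × 41 = 82, the number needed before loss to follow-up, where the sample-size section requires 2 × 51 = 102 to be enrolled

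*Protocol article*

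**What the plan says.** Two neighbouring sections of the protocol article give different numbers.

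- **Sample size [14].** The calculation ends with "This resulted in a total sample size of 82 patients", that is 2 × 41. The next sentence adds attrition: "With an accounted lost to follow-up of 20%, a sample size of 102", that is 2 × 51, "is necessary to prove statistic group differences".
- **Sequence generation [16a].** The plan is described as already made: "We created a randomization plan using a computer-generated randomization schedule". It is called simple and balanced. After the 1:1 ratio, a bracket gives the group sizes as 2 × "41 for SMART and NORMT). Subsequent allocation is provided in a separate document".

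Three other sections bear on which number belongs in the allocation section.

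- **Recruitment [15]** makes MRI confirmation the step that leads to randomisation and inclusion. **Participant timeline [13]** puts allocation at t1, before the intervention.
- **Handling of non-adherence and missing data [20c]** removes withdrawn participants from the analysis of the primary aim.
- **Concealment mechanism [16b]** and **Implementation [16c]** assign sequence generation, enrolment and assignment to different sport scientists.

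No section describes replacing patients who drop out or extending the list.

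**The concern.** The 20% allowance is for loss after randomisation, so everyone enrolled needs an assignment, including those later lost. The number to randomise is therefore 102, and 82 is what should remain for analysis. The allocation section prints 82.

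A schedule that balances two arms has to be generated for some definite total, so a group size given in this section is naturally read as the size of the plan. On that reading, one of two things follows. Randomisation may stop at 82, and the analysis then falls short of the number the protocol says it needs. Or enrolment continues to 102, and the last 20 patients are assigned by a procedure the protocol does not describe.

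**Working it through.** **Inputs from the protocol article.** Sample size [14] gives 82 before loss, 20% loss, 102 to enrol, "effect size *f* = 0.5", α = 0.05, and power of "0.80), two groups (SMART and NORMT), and four measurements". Sequence generation [16a] gives 2 × 41.

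**Step 1: reproduce the enrolment target.** Number to enrol = number needed ÷ (1 − loss) = 82 ÷ 0.80 = 102.5. The stated 102 agrees within rounding (102 × 0.80 = 81.6). The 102 is therefore the 82 inflated for loss, and the two numbers have different roles.

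**Step 2: compare with the allocation section.** 2 × 41 = 82 and 2 × 51 = 102. The difference is 102 − 82 = 20 patients, 10 per arm.

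**Step 3: what remains if only 82 are randomised.** 82 × 0.80 = 65.6, about 66 in all or 33 per arm. The shortfall against the protocol's own 82 is 82 − 66 = 16. This step uses only figures in the protocol.

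**Step 4: what that shortfall costs in power.** The protocol does not state which repeated-measures test was powered or what correlation between measurements was used, so these must be assumed. For the between-group test with m = 4 measurements and correlation ρ, the noncentrality is

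λ = f² × N × m ÷ (1 + (m − 1)ρ), with 1 and N − 2 degrees of freedom.

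First, can 82 be reproduced?

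| Effect size | Test | ρ | N for power 0.80 |
|---|---|---|---|
| f = 0.5 (stated) | between groups | 0 to 0.9 | 12 to 32 (22 at ρ = 0.5) |
| f = 0.5 (stated) | group by time | 0 to 0.9 | 14 down to 4 |
| f = 0.25 (assumed) | between groups | 0 to 0.9 | 34 to 120 (82 at ρ = 0.5) |
| f = 0.25 (assumed) | group by time | 0 to 0.9 | 46 down to 8 |

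The stated f = 0.5 does not lead to 82 under either test. Of the settings tried, only the between-group test with f = 0.25 and ρ = 0.5 gives exactly 82.

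Power of the between-group test at ρ = 0.5 is then:

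| | N = 82 | N = 66 |
|---|---|---|
| f = 0.25 | λ = 0.0625 × 82 × 4 ÷ 2.5 = 8.2; power 0.808 | λ = 0.0625 × 66 × 4 ÷ 2.5 = 6.6; power 0.716 |
| f = 0.5 | λ = 0.25 × 82 × 4 ÷ 2.5 = 32.8; power above 0.99 | λ = 0.25 × 66 × 4 ÷ 2.5 = 26.4; power above 0.99 |

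The Outcomes section defines the primary comparison as a difference in change, which is closer to a group-by-time test. For that test at f = 0.25 and ρ = 0.5, power with 66 is also above 0.99.

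**The case against.** **The list length is not stated.** The bracket follows the allocation ratio and repeats the pre-attrition figure from the sample-size section. The assignments themselves are in a document that cannot be seen here. The figure may simply have been carried over while the actual list runs to 102 or more. This stands: a reader might infer that patients 83 to 102 certainly have no assignment, and the text does not establish that. It does establish that the printed number disagrees with the enrolment target.

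**The trial is not shown to be underpowered.** A reader might infer that stopping at 82 leaves power near 0.72. That figure needs f = 0.25 and a correlation of 0.5, and neither is in the protocol. At the stated f = 0.5 the loss is negligible. This also stands. What can be said without added assumptions is that about 66 is below the 82 the protocol sets for itself. That 82 does not follow from f = 0.5 is a separate problem in the sample-size section and adds no weight here.

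**Extending the list need not harm concealment.** A reader might infer that adding 20 assignments in an open, single-centre trial would expose them. The protocol keeps the list from the enroller and separates the roles, so an extension made by the same separate generator can be concealed as well as the first 82. No harm to concealment is shown. What remains is that no extension is described.

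**The rest may be in the full protocol.** An article may leave detail elsewhere, but this is a conflict between two printed figures and not an omission.

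**Conclusion.** The inconsistency is real and needs correcting. The allocation section gives 82 where the protocol's own calculation requires 102, a gap of 20 patients.

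The consequences are conditional. If the list ends at 82, either about 66 evaluable patients remain against a requirement of 82 (assuming the protocol's 20% loss and no replacement), or 20 of 102 patients have no pre-generated assignment. If the list is longer, only the text is wrong.

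The effect on power ranges from negligible at the stated f = 0.5 to a fall from about 0.81 to 0.72 at the assumed f = 0.25 and correlation 0.5. The document does not allow a choice between these.

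**What to change.** 1. Check how many assignments the existing list contains.
2. Correct Sequence generation [16a] to 2 × 51 = 102, in line with Sample size [14].
3. If the list is short, have the separate sequence generator produce the remaining 20 balanced assignments, 10 per arm, before patient 83 is due. Keep them from the enroller under the arrangements in sections 16a to 16c.
4. Trial status estimates that recruitment ends in January 2024. If patient 83 has already been randomised, record how and when the later assignments were made.

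The cost is a one-line correction and, at most, a short addition to the list. No patients are needed beyond the 102 already planned.

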### Concealment mechanism [16b]

Allocation is concealed since two separate sport scientists are responsible for randomization and the participant enrolment, respectively. The information about the treatment allocation will be given to the sport scientist who is performing the diagnostics not until t1. Therefore, there is no influence on the assignment.

### Implementation [16c]

The generating of the allocation sequence, enrollment of the participants, and assignment of the participants to the interventions will be all done by separate sport scientists.

## Assignment of interventions: blinding

### Who will be blinded [17a]

Since the two interventions are completely different in their implementation, the intervention is impossible to blind. We are aware that there might be some bias due to this. Statistical analysis will be blinded, since it will be performed by a biostatistician.

### Procedure for unblinding if needed [17b]

Not applicable.

## Data collection and management

### Plans for assessment and collection of outcomes [18a]

#### Primary outcome

The *CAIT* is a questionnaire to get a subjective insight into regional functional impairments following LAS. It consists of 9 items measuring the severity of functional ankle instability [44]. The total score ranges from 0 to 30 with 0 representing a painful and strongly instable ankle during low-intense everyday activities and 30 representing a pain-free and subjectively stable ankle. Furthermore, the CAIT score is one out of three criteria, established by the International Ankle Consortium, to define CAI [8]. The Minimal Clinical Important Difference (MCID) of the CAIT is reported to be ≥ 3 points [43].

#### Secondary outcome

The *FAAM* is a questionnaire to assess the subjective impairments of ankle joint function [45]. It has 29 items divided into two subscales, a 21-item Activities of Living Subscale, and an 8-item Sport Subscale. Higher scores represent higher levels of function for each subscale, with 100% representing no dysfunction. The MCIDs are 8 and 9 points, respectively [46].

The questionnaires (CAIT and FAAM) are assessed by the web-service of Heartbeat medical (https://heartbeat-med.com/de/), which collects patient data via tablet, or any device at home (via email invitation). Biomechanical tests take place in the motorics laboratory “Athletikum Rhein Ruhr” affiliated to the department for arthroscopic surgery, sportstraumatology, and sportsmedicine, BG Klinikum Duisburg.

*Gait and run analysis* will be performed at 5 and 10 km/h, respectively. The analysis time interval will be 30 s each. Inertial measurement units (IMU) and EMG sensors are attached to measure three-dimensional kinematic data as well as muscle activity (see detailed descriptions below). The gait and run analyses take place on a motorized treadmill (h/p/cosmos sports & medical GmbH, Nussdorf-Traunstein, Germany) with an integrated pressure plate (FDM-THQ 2i, Zebris medical GmbH, Isny, Germany) sampling data at 300 Hz.

*Static postural control* is measured on the pressure plate of the treadmill. Trials of single-leg stance with eyes open and closed are performed with each leg (10 s each) (Fig. 2). For analysis, the COP is measured. We will track the COP area (mm^2^), mean COP velocity (mm/s), and the COP excursion length (mm). Additionally, there will be TTB analysis during the assessment of static balance. TTB measures estimate the time it would take for the COP to reach the boundary of the base support (individual foot boundaries) if the COP would continue to move on its trajectory at its instantaneous velocity. A lower TTB indicates greater postural instability as the COP is reaching its boundary of the base support faster [13]. Trials are repeated if the participants lose balance during the single-leg stance.

**Fig. 2 Fig2:**
[figure not shown]
Single-leg stance

*Dynamic postural control* is assessed via the mod. SEBT. Measurements (cm) are taken in the anterior, posterior-medial, and posterior-lateral reach direction. A standardized test kit is used. The kit consists of Y-shaped tubes connected by a central platform. Boxes placed on each tube allow the patient to slide into all three reaching directions allowing to assess reach distance by scales attached to the tubes (Fig. 3). The participants maintain a single-leg stance with their heels placed firmly on one of the three boxes of the test kit while sliding with the first of the other three boxes with the opposite leg as far as possible. Absolute differences between both legs as well as the composite score (summed average of right/left anterior, posterior-medial, and posterior-lateral values normalized to leg length) are determined.

**Fig. 3 Fig3:**
[figure not shown]
Modified Star Excursion Balance Test

There are two types of *jumps* that are assessed: single-leg drop landing and bilateral drop-jump. Both jumps are performed from a 20 cm and 30 cm box onto two parallel independent force plates (FP-4060–08, Bertec Corporation, Columbus, Ohio, USA) to measure vertical ground reaction force. Data is sampled at 1500 Hz with a standard bandwidth filter of 500 Hz. The bilateral dropjump is a reliable test which is mainly determined by a person’s capability to utilize muscle–tendon elastic energy storage to generate force and can be used to assess maximum strength output, rate of force development and stiffness [47]. The participants are instructed to have a minimal ground contact time followed by a maximal rebound jump (Fig. 4).

**Fig. 4 Fig4:**
[figure not shown]
Dropjump

For the single-leg drop landing, the participants are instructed to drop forward onto the force plate, landing on one leg, resume, and hold a steady position for approximately 3 s. In both jumps, the participants are instructed to keep their hands fixed at their hips (Fig. 5). During the jump execution, it is important that the participants land within the boundaries of the force plates. If not, the jump will be repeated. There are going to be three single-leg drop landings for each side and per height as well as three drop-jumps per height. IMU and EMG sensors are attached to measure three-dimensional kinematic data as well as muscle activity (see detailed description below).

**Fig. 5 Fig5:**
[figure not shown]
Single-leg drop landing

The *strength* diagnostic will be performed in a motorized dynamometer (IsoMed, D. & R. Ferstl GmbH, Hernau, Germany) which is able to measure bilateral force (N) production in a closed kinetic chain as well as plantarflexion and dorsiflexion torque (Nm) in an open kinetic chain. There will be isometric as well as isokinetic (concentric/eccentric) lower limb strength measurements and measurements of the plantar- and dorsiflexors (concentric/eccentric and eccentric/concentric). For all tests, the participants will be fixated with two shoulder restraints, one waist strap, and an additional restraint over the distal thigh during the plantarflexion/dorsiflexion to secure them firmly to the dynamometer and prevent compensatory movement.

The legpress measurements include maximal isometric voluntary contractions (3 repetitions with 1 min rest) at 90° hip flexion, 90° knee flexion, and neutral foot position which is determined using a handheld goniometer as well as a dynamic (concentric extension/eccentric extension) test protocol (6 repetitions) with a range of motion (ROM) from 90° knee flexion to approximately 10° knee flexion (determined using handheld goniometer). The movement speed is set to 120 mm/s (Fig. 6).

